## Abstract

Persons with primary progressive aphasia (PPA) often experience limitations in their quality of life (QoL). Some studies have shown positive effects of speech and language therapy on QoL in persons with PPA. However, there is still a lack of evidence for disorder-specific approaches for this important therapeutic goal. The biographic-narrative approach (narraktiv) has been shown to significantly improve QoL in persons with post-stroke aphasia. In the planned study, the biographic-narrative approach will be adapted for persons with PPA (Cope PPA), and its efficacy will be investigated. First, a focus group interview with five persons with PPA will be conducted to identify the wishes and needs of participants. Based on the results, the narraktiv manual according to Corsten et al. (2015) will be revised. Second, an efficacy study will be conducted according to the new Cope PPA manual with 24 persons with PPA in a waiting group control design. The primary outcome, QoL, will be assessed using questionnaires (Stroke and Aphasia Quality of Life Scale-39) and semistructured interviews. Depressive symptoms, life satisfaction and cognitive/communicative functioning will also be assessed. If Cope PPA proves efficacy, this study may help to improve the treatment of persons with PPA.

## 1. Introduction

Primary progressive aphasia (PPA) is a rare clinical syndrome characterised by prominent speech disorder and an average prevalence of 3:100,000 [1,2]. It is classified into three variants (nonfluent, semantic, and logopenic) and is associated with Alzheimer’s pathology or frontotemporal dementia [3,4]. As the age of onset is approximately 65 years [3], it has a devastating impact on the professional and private roles of an affected person [5]. The treatment of PPA is limited to mitigating symptoms, as no curative therapy is known to date [6]. About 40% of persons with PPA develop depression as a comorbidity during the course of the disease, which can be attributed to a perceived awareness of the individual situation and to an impaired self-image of a person with a speech disorder [7,8,9]. Since aphasia limits access to psychotherapeutic services [10], approaches that enhance quality of life (QoL) are increasingly being considered by speech and language therapists (SLTs). Further, QoL, which is defined by the World Health Organisation (WHO) as an individual’s perception of their position in life considering cultural and personal context factors in relation to personal goals and concerns [11], is described as the “ultimate” outcome of aphasia therapy [12]. Psychoeducational group programs and participatory approaches have already been successfully applied to persons with PPA and are valued by individuals [13,14]. Counselling and communication partner training showed positive effects on coping with illness and communication in dyads [15,16]. However, there is uncertainty in the application of QoL-related methods in persons with PPA and a lack of high-quality studies proving effects on QoL of this target group [7,17].

In a systematic review summarising rehabilitative interventions for the prevention and treatment of depression in poststroke aphasia patients, the authors refer to a mixed-methods study by Corsten et al. (2015) [18].

This study is emphasised as the one with the highest quality and level of evidence for persons with poststroke aphasia and demonstrates the effects of the biographic-narrative approach narraktiv [18,19]. The narraktiv intervention contains five individual and seven group therapy sessions in which biographic storytelling is stimulated. This approach is based on the idea that aphasia hinders the natural and daily redevelopment of identity, as the medium for identity work (communication) is impaired. Disturbed identity work leads to a negative self-image and thus reduces QoL. Supporting narration can help persons with aphasia to work on their identity and to build a sense of coherence, ultimately improving their QoL [9,20,21]. The participants in the narraktiv intervention were persons with poststroke aphasia who did not have depression or who exhibited early signs of depression. Significant improvements with small to medium effect sizes were observed in improvement of mood and health-related QoL, measured by the Visual Analogue Mood Scale (VAMS, [22]) and the Aachen Life Quality Inventory [23]. The effects remained stable over a period of three months after the intervention or even increased towards follow-up, as in the case of the Aachen Life Quality Inventory scores. Since many therapeutic approaches can be transferred from persons with poststroke aphasia to persons with PPA [6], it seems promising to apply the concept of the biographic-narrative approach narraktiv according to Corsten et al. (2015) to persons with PPA.

Comparable approaches such as ‘simple reminiscence’, ‘life-review’, or ‘life-review therapy’ [24,25] have been used successfully in patients with dementia and older persons [24,26,27,28]. While ‘simple reminiscence’ focuses on the recall and sharing of memories, ‘life review’ is more evaluative and aims to cover the whole life story chronologically. ‘Life-review therapy’ is a continuation of ‘life review’, in which more elements of cognitive therapy are used to give persons a more positive view of their lives [26]. Although ‘simple reminiscence’ can be conducted in a nursing home setting by counsellors with basic skills, ‘life review’ should be directed towards individuals with mild psychological distress and delivered by counsellors with advanced skills. In cases of serious psychological distress, experienced counsellors could use ‘life-review therapy’ [25]. Another way to differentiate between the approaches is to categorise them as structured or unstructured therapies [29]. The narraktiv intervention is most likely to be categorised between structured/unstructured approaches and combines aspects of ‘simple reminiscence’, ‘life review’, and ‘life-review therapy’. On the one hand, it is highly structured for the therapist through predetermined question types and a fixed structure of individual and group therapy sessions; on the other hand, it is nondirective. For example, participants are free to decide what they want to tell about their own lives and what personal relevance they want to have, thanks to the open-narrative stimulus. The biography does not have to be presented in every detail, neither chronologically nor in terms of content. The focus on persons with aphasia distinguishes the biographic-narrative approach from reminiscence or life-review therapy, which were developed for persons with memory deficits rather than for persons with primary aphasia [30].

Due to its person-centred focus on QoL, narraktiv differs from the participation- and environment-based group programmes that try to enhance QoL indirectly and have been evaluated for persons with PPA to date [13,31]. Because of the non-directive character, the approach also differs from counselling services that have been evaluated for use with persons with PPA and their caregivers [15]. As far as we are aware, there is only one case study indicating the use of narraktiv in a person with an advanced nonfluent variant of PPA in a palliative care setting [32]. The adjustments and effects of narraktiv are not described by the authors [32]. However, it seems close at hand that the original narraktiv intervention which is categorised by experts as a rehabilitative care intervention [18], needs to be adapted for persons with PPA who may have other needs against the background of cognitive deficits and the progression of the disease. Participatory research enables development according to a bottom-up principle [33]. In our study, it will be used to make the approach more sustainable and acceptable.

The aim of the present study is to prove the transferability of the biographic-narrative approach to the treatment of persons with PPA. In a focus-group interview, the potential need to adapt the biographic-narrative approach narraktiv according to Corsten et al. (2015) for persons with PPA will be discussed. An efficacy study will then be conducted to evaluate the efficacy of the adapted biographic-narrative approach Cope PPA for persons with PPA and to explore the effects in individual cases.

The research questions are as follows:What need for adaptation do persons with PPA see for the biographic-narrative approach narraktiv for use with persons with PPA?Does the adapted biographic-narrative approach Cope PPA improve the QoL of persons with PPA?

## 2. Materials and Methods

In the following, the method of the planned study is reported considering the SPIRIT checklist. This international checklist contains 33 evidence-based recommended items, reflecting the minimum content of a clinical trial protocol (2013, see Additional Supplementary Materials File S1). The current study is monocentric, as it will be conducted only at the outpatient memory clinic at the Department of Psychiatry and Psychotherapy of the University Hospital Mainz (Mainz, Germany). The study complies with the General Data Protection Regulations and will be conducted in accordance with the Declaration of Helsinki. This study was approved by the Ethics Committee of the Federal Medical Association of Rhineland-Palatinate (2023-17294).

### 2.1. Inclusion and Exclusion Criteria

Only persons who fulfil the clinical diagnostic consensus criteria for PPA according to Gorno-Tempini (2011, [4]) will be included in both phases of the study. Persons with all variants of PPA are eligible. Although persons with all stages of PPA can be included, participants must be willing to work in a group and be able to communicate basic thoughts. People with mutism were therefore excluded from both phases of the study. According to the consensus criteria [4], persons were excluded if their speech deficits could be better explained by other neurological disorders like stroke or brain injury. Further exclusion criteria were inadequate visual acuity despite correction with a visual aid and inadequate hearing despite the use of a hearing aid.

The ability to give consent is a prerequisite for participation in both phases of the study. For persons with dementia syndromes such as PPA, there may be uncertainties in clarifying the ability to consent [34]; for this reason, the following criteria of the guideline ‘capacity to consent of persons with dementia’ are used for this purpose [35]. The consent of the participants will be obtained in detail and in an understandable form by the deputy study director ([name]) and study doctors involved ([name], [name]) before the start of the study, taking into account the linguistic, cognitive, and emotional competences of each participant. Immediately before each assessment and therapy session, the ability to give consent will be reassessed and documented by the research team based on the following criteria: (1) understanding relevant information, (2) understanding the implications for one’s own situation, (3) reasoning about the information, and (4) expressing a treatment choice [34,36]. Participants will give their informed consent to participate and to be video-recorded during the assessments and the therapy sessions. The participants’ faces will be fully visible to account for the participants’ facial expressions as a form of communication. For the efficacy study, caregivers will give their informed consent for being interviewed at the end of the intervention.

Persons with pronounced cognitive deficits, corresponding to a score < 10 out of 30 points in the established cognitive screening test Mini Mental-State Examination (MMSE, [37]), will be excluded at the beginning of the efficacy study, as there are indications from the literature that more complex questionnaires cannot be answered in cases of severe cognitive impairment [38]. Individuals whose cognition deteriorates to <10 points on the MMSE over the course of the study will not immediately be excluded. In these cases, an individual decision will be based on clinician ratings and according to the participants’ wishes.

Furthermore, the presence of severe depressive symptoms (clinical diagnosis and/or severe depressive symptoms, corresponding to >35 points on the Montgomery–Åsberg Depression Rating Scale (MADRS, [39]) is defined as an exclusion criterion at the beginning of the study because narraktiv was developed for preventing the occurrence of depression and has not been evaluated for the treatment of this condition [19]. However, due to the positive effects of participating in peer support groups on depression, persons with mild to moderate depression will not be excluded from the present study [40]. If participants show signs of depression in the course of the study (MADRS > 35 at t1–t3 or characteristics of a depressive disorder such as physical exhaustion, appetite disorders, changes in gestures/facial expressions or physiognomy during the therapy sessions), suicidal tendencies will be explored and documented in an individual setting. Questions from the national guideline “Unipolar depression” will be used for this purpose, e.g., “Have you had or do you have concrete plans to harm yourself?” and “Is there anything that keeps you alive?” [23]. If acute suicidal behaviour is suspected, an emergency psychiatric counselling will be conducted at the Department of Psychiatry and Psychotherapy of the University Hospital Mainz. If there is no acute suicidal tendency, the person will be promptly seen by a specialist in the outpatient memory clinic and the research team will plan further treatment steps if necessary. Participation in the study will be in addition to any other treatment participants may receive.

Whether persons with PPA previously received or currently receive speech and language therapy will not be a criterion for inclusion or exclusion in our study.

### 2.2. Identification and Recruitment of Participants

Participants will be recruited via the outpatient memory clinic as well as by cooperating practices and outpatient speech and language therapy practices. A recruitment flyer has been created in understandable, simple language to inform participants about the study. Prior to participation, potential participants will be screened through face-to-face counselling.

### 2.3. Design

The planned study consists of two phases using an adaptive clinical trial design. ‘Phase one’ envisages a focus-group interview in which five persons with PPA will take part. The aim of the focus-group interview is to identify specific needs of persons with PPA for adaptation of the biographic-narrative approach narraktiv for use with persons with PPA. The ‘phase one’ corresponds to a qualitative exploratory study based on the principle of a group discussion, aiming to generate data based on social interaction involving persons with PPA in the study process in the sense of participatory research [41]. In ‘phase two’, an efficacy study will be conducted with 24 persons with PPA evaluating the adapted biographic-narrative approach Cope PPA. The efficacy study will be a mixed-methods randomised controlled trial with a waiting group, which is a suitable control (compared to standard care) for the inconsistent approach in the treatment of persons with PPA (Figure 1).

#### 2.3.1. Blinding

Due to the nature of the intervention, blinding of the investigators and participants is not possible. In ‘phase one’, independent raters are involved in the transcription and coding of the interviews. In ‘phase two’, external judgement assessments are evaluated by independent raters who can use the video recordings as the basis for the evaluation.

#### 2.3.2. ‘Phase One’: Focus-Group Interview

In the focus-group interview, the participants will be interviewed about their expectations/wishes for speech and language therapy and individual strategies for coping with their diagnosis (see Figure 2). Furthermore, the procedure and methods of narraktiv will be introduced. Persons with PPA will be asked to assess the extent to which methods and materials (e.g., use of pictograms or photographs) appear feasible and useful. The interviewer is a trained SLT ([name]) who has some experience in conducting group discussions with aphasic participants. Repair behaviour such as repetition, revision/reformulation and cueing [42] are used to support participants’ communication. Turn-taking is organised by the interviewer. A text card saying “We listen to each other and let each other talk” is provided as a communication rule for the interview. If necessary, the participants are reminded of this agreement. The guidelines for the focus group interviews are provided in Additional File Supplementary Materials File S2.

#### 2.3.4. Randomisation

The division of the participants into groups is necessary for conducting the efficacy study and will be carried out as a random allocation by the deputy study director ([name]) [46]. Since the therapy groups will consist of six participants, four blocks must be formed (N = 24). A permutation of the four blocks will be drawn at random, with the first half (*n* = 12) of the permutation being assigned to the therapy group and the second half (*n* = 12) assigned to the waiting group (see Figure 4). Each allocation thus applies to six consecutive participants. Groups will be randomised without balancing.

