#### 2.3.5. Sample Size Justification

It can be assumed that the effects in persons with PPA are comparable to the effect sizes in persons with aphasia after stroke, as the impairment patterns are similar [42], and many approaches for the treatment of poststroke aphasia are successfully transferable to PPA [6,47]. Based on the results of Corsten et al. (2015), who reported an 85.19% improvement in Complaints and an 88.89% improvement in Burden score on the Aachen Life Quality Inventory [23] from baseline to follow-up, with an overall low to moderate effect size (d = 0.22 to 0.58) [19], an a priori power analysis was conducted using G*Power 3.1.7. This resulted in a total sample size of 24 for an estimated effect size of f = 0.275 (d = 0.55; α = 0.05; power = 0.8). It is assumed that with this sample size, effects can be detected in persons with PPA who are examined with the Stroke and Aphasia Quality of Life Scale-39 (SAQOL-39, [48]). It is possible that the effect sizes in persons with PPA are even greater if persons with mild depression are included; thus, a lower baseline score for QoL can be expected.

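### Only four blocks of six are randomised, two per arm; the sample size makes no allowance for this and the planned ICC check has no stated consequence

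*Protocol article*

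**What the plan says.** Section 2.3 describes the second phase as individual-sounding: "The efficacy study will be a mixed-methods randomised controlled trial with a waiting group". Section 2.3.4 then sets out how allocation works. The size of the therapy groups is given as the reason for forming blocks: "Since the therapy groups will consist of six participants, four blocks must be formed (N = 24"). Next, "A permutation of the four blocks will be drawn at random". The first two blocks in the drawn order go to therapy and the last two to waiting, 12 people each. The section draws the consequence itself: "Each allocation thus applies to six consecutive participants". It adds: "Groups will be randomised without balancing".

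Section 2.3.5 bases the sample size on an "effect size of f = 0.275 (d = 0.55; α = 0.05; power = 0.8") and reports: "This resulted in a total sample size of 24". It does not mention blocks or therapy groups.

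Section 2.4.3 plans an ANOVA for the primary outcome, with before-after and between-arm comparisons. It says that dependence in the data will be examined with an intraclass correlation coefficient, but not what follows from the result. Section 2.4.5 makes a significantly larger SAQOL-39 gain from t0 to t1 in the therapy group one of the success criteria.

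**The concern.** The unit that is randomised is the block. No participant's arm is drawn separately from that of the other five in the block. That is cluster randomisation with two clusters per arm, although the trial is sized as if it had 24 independent participants.

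Two things are at stake. First, anything that makes one run of six change differently from another over the ten weeks from t0 to t1 is carried into the arm difference, and two blocks per arm give almost no information to tell it apart from treatment. Sections 2.1 and 2.2 admit all PPA variants, all stages short of mutism and several recruitment routes, so runs of six could differ, and nothing balances them. Second, a significant between-arm result would depend on an independence assumption that the randomisation does not supply. A later analysis plan cannot supply it either, because analysis does not add randomised units.

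**Working it through.** **Inputs.** From sections 2.3.4 and 2.3.5: N = 24; 4 blocks of 6; 2 blocks per arm; f = 0.275 (d = 0.55); α = 0.05, sidedness not stated; power 0.8. From section 2.4.5: the between-arm criterion is the change from t0 to t1. Assumed, because the article does not give them: the correlation ρ between repeated measurements, the number of measurements m used in the power calculation, and the ICC within blocks.

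**1. The plan's own figure.** Repeated-measures ANOVA, group-by-time interaction, k = 2 groups: λ = f²·N·m/(1 − ρ), with df (k − 1)(m − 1) and (N − k)(m − 1). Here f² = 0.075625.

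- m = 3, ρ = 0.5: λ = 0.075625 × 24 × 3 / 0.5 = 10.89; power 0.822, and N = 24 is the required size.
- m = 2, ρ = 0.6: λ = 0.075625 × 24 × 2 / 0.4 = 9.075; power 0.821, again N = 24.
- m = 2, ρ = 0.5: λ = 7.26; power 0.73 at 24, and N = 30 would be required.

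So 24 can be reproduced under plausible settings, and those settings treat the participants as independent. A plain two-sample comparison at d = 0.55 would need about 52 per arm.

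**2. Allocations.** C(4,2) = 6, equally likely. A randomisation test therefore cannot give less than 1/6 = 0.167 one-sided or 2/6 = 0.333 two-sided, since each split has a mirror image.

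**3. Recruitment order.** With participants numbered 1 to 24 in order of enrolment:

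| Blocks in therapy | Mean position, therapy | Mean position, waiting | Difference |
|---|---|---|---|
| 1, 2 | 6.5 | 18.5 | −12 |
| 1, 3 | 9.5 | 15.5 | −6 |
| 1, 4 | 12.5 | 12.5 | 0 |
| 2, 3 | 12.5 | 12.5 | 0 |
| 2, 4 | 15.5 | 9.5 | +6 |
| 3, 4 | 18.5 | 6.5 | +12 |

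Arm coincides fully with recruitment half in 2 of 6 draws, is shifted by 6 places in 2 of 6, and has equal mean position in 2 of 6.

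**4. Effect of clustering.** Design effect = 1 + (6 − 1)·ICC; effective N = 24 / design effect. The type I error is that of a 12 versus 12 t-test ignoring blocks at nominal 5% (100,000 simulated trials per ICC, two blocks of six per arm, no treatment effect).

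| Assumed ICC | Design effect | Effective N | True type I error |
|---|---|---|---|
| 0.02 | 1.10 | 21.8 | about 6% |
| 0.05 | 1.25 | 19.2 | about 8% |
| 0.10 | 1.50 | 16.0 | about 11% |
| 0.20 | 2.00 | 12.0 | about 18% |

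**5. A test that respects the blocks.** Four block means in two arms leave 4 − 2 = 2 df, with critical t 4.30 against 2.07 on 22 df. For the t0 to t1 interaction (m = 2, ρ = 0.5), the noncentrality is √(7.26 / design effect). Power is about 0.33 at ICC 0 and about 0.20 at ICC 0.20, against 0.73 for 24 independent participants under the same settings.

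**6. The alternative.** Randomising 6:6 within each of two sets of 12 gives C(12,6)² = 924² = 853,776 allocations. Randomising 12:12 among all 24 gives C(24,12) = 2,704,156.

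**The case against.** Several points stand against a stronger reading.

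- A reader might infer that arm is simply confounded with recruitment period. Complete overlap occurs in only a third of draws, and in another third the mean positions are equal. Calendar time matters only if enrolment is staggered. Section 2.3.3 has two groups starting therapy immediately after randomisation, which fits a single draw once all 24 are enrolled; Figure 4 is not available to settle it. With a single draw, calendar confounding largely disappears, but there are still four randomised units.
- A reader might infer that no significant result is possible. The floor of 0.33 belongs to a randomisation test, and the article plans an ANOVA, which can fall below 0.05. What the ANOVA lacks is support from the randomisation.
- A reader might infer that dependence is ignored. Section 2.4.3 does plan an ICC, although it is unclear whether for blocks, therapy groups or repeated measurements. With two blocks per arm it is barely estimable, and no consequence is stated. Exact model terms may be in a fuller plan, but these cannot change the number of units.
- Baseline severity is not hopelessly entangled with treatment. The criterion is change, which removes stable level differences, and the MMSE and scenario test are measured at t0. Therapist experience is also a poor example, since the waiting group receives no study therapy before t1. What remains is block-level variation in change.
- The pre- to post-intervention success criterion does not depend on the between-arm allocation.

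The harm therefore runs from small to serious, depending on an ICC that nobody has stated.

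**Conclusion.** The point holds in this form. As written, the between-arm comparison has 4 randomised units and 6 possible allocations, while N = 24 assumes independent participants and the ICC check leads nowhere stated. The unit count follows directly from section 2.3.4 and needs no assumption. The type I error of about 6% to 18% rests on assumed ICCs of 0.02 to 0.20, and the power figures also on ρ = 0.5 with two measurements. Overlap with recruitment half is a possibility (2 of 6 draws) that matters for calendar time only under staggered enrolment. It should be put right before allocation: it weakens the only randomised contrast, cannot be repaired afterwards, and is not needed to obtain therapy groups of six.

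**What to change.** Replace the block permutation in section 2.3.4. After t0, randomise individuals 6:6 to therapy and waiting within each consecutive set of 12, or 12:12 if all 24 are enrolled first; then form therapy groups of six within each arm. The 12:12 split and the group size stay as they are.

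In section 2.4.3, include the cohort of 12 as a factor where cohorts are used, and say how clustering by therapy group enters the analysis. Individual randomisation does not remove that clustering: participants are still treated together in sixes, and between t0 and t1 only the therapy arm is. With just two therapy groups in that arm its size will be poorly estimated, so results over a range of assumed ICCs would help. In section 2.3.5, state that the power figure assumes independent participants.

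Cost: changes of wording, with no extra patients or staff. If enrolment is staggered, a therapy group starts once 12 rather than 6 people are enrolled. That is a real delay for early recruits with a rare, progressive condition at a single centre. If all 24 are enrolled before the draw, there is no delay.
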